### Sample size

2.6

The sample size was calculated using the two-sample t-test method in PASS 15 software (NCSS, LLC, Kaysville, Utah, USA), with a two-sided significance level of 0.05 and a power of 0.8. Based on preliminary clinical observations obtained in our center, topical FEO alone was effective in approximately 50% of patients with BSP. This finding, combined with a conservative estimate of efficacy, prompted a reassessment of the required sample size to ensure adequate statistical power. The revision was implemented after trial initiation but prior to completion of participant recruitment, and constitutes an important protocol modification based on internally generated data. To determine the mean and standard deviation (SD) needed for the sample size calculation, we retrospectively analysed data from 61 patients with BSP at our movement disorders clinic who had received standard BoNT-A treatment and met the study’s inclusion criteria. After receiving their last three consecutive BoNT-A injections, these patients experienced clinical benefits for less than 3 months each time, demonstrating consistently unsatisfactory therapeutic effects. The mean duration of clinical benefits was 73.99 days (SD = 14.28). Given that the control group will receive a placebo, there may have been greater variability in the therapeutic effects due to individual response and disease progression; therefore, we decided to round the mean value to 75 days and the SD to 15 (i.e., 75.0 ± 15.0) to ensure robustness in the calculation. In this study, we hypothesized that combining BoNT-A injection with topical FEO would extend the effective duration of symptom relief by 30 days to 105.0 ± 15.0 days. Given an expected effective rate of only 50%, we estimated the mean duration of benefit in the experimental group as 90.0 ± 18.5 days, reflecting a weighted average between responders and non-responders. The resulting sample size calculation indicated N1 = N2 = 25, meaning that 25 participants are required for each group. Considering the participant loss to follow-up, we determined that each group would recruit 32 participants. A professional statistician verified the sample size calculation method. The amended protocol was reviewed and approved by the Ethics Committee of the First Affiliated Hospital of Sun Yat–sen University.

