### Randomization and recruitment

2.7

The randomization procedure will be managed and documented entirely by an independent statistician who is not engaged in the implementation of the study. Sixty-four random numbers were generated using IBM SPSS Statistics (v.25.0; IBM Corp., Armonk, NY). These random numbers will then be allocated equally to two groups using the visual split-box function in SPSS. Another designated blinded investigator is responsible for assigning participants to different interventions. To ensure allocation concealment, other investigators, including participant recruiters and evaluators, will remain unaware of the randomization results until the study is fully completed. Using this approach, the study will effectively accomplish randomization and allocation concealment, thereby minimizing selection bias and ensuring the validity and reliability of the results.

The intended recruitment period is approximately 2 years and 2 months, from 28 December 2024, to 28 February 2027. The participants will be free to withdraw from the study at any time. The reasons for withdrawal will be documented. If the reason is associated with adverse events, it will be followed up until the issue is completely resolved. Participants who have received other treatments or participated in another program related to BSP therapy during the trial will be considered dropouts.

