### Trial assessment and follow-up

2.9

Full eligibility criteria will be assessed and confirmed before randomization. Further assessments should be conducted at multiple time points. An overview of the data collection process is provided in Table 2. Data will be collected from all participants until they complete the 24-week follow-up period or discontinue the study.

**Table 2 tab2:** Time and events.

Description	Screening	Day 0	2nd week	4th week	8th week	12th week	16th week	20th week	24th week
Consent	**√**								
Neurological exam	**√**								
Medical history	**√**								
Inclusion/exclusion	**√**								
Randomization	**√**								
MRI	**√**								
Baseline assessment	**√**								
Motor symptom assessment	**√**		**√**	**√**	**√**	**√**	**√**	**√**	**√**
Quality-of-life assessment	**√**		**√**	**√**	**√**	**√**	**√**	**√**	**√**
Video recording	**√**		**√**	**√**	**√**	**√**	**√**	**√**	**√**
PEGR			**√**	**√**	**√**	**√**	**√**	**√**	**√**
Non-motor symptom assessment	**√**					**√**			**√**
Blinded rater evaluation	**√**	**√**	**√**	**√**	**√**	**√**	**√**	**√**	**√**
BoNT injection		**√**							
FEO/CO application			**√**	**√**	**√**	**√**	**√**	**√**	**√**
Clinical assessments	**√**	**√**	**√**	**√**	**√**	**√**	**√**	**√**	**√**
Safety assessment	**√**	**√**	**√**	**√**	**√**	**√**	**√**	**√**	**√**

BoNT, botulinum toxin; CO, coconut oil; FEO, frankincense essential oil; MRI, magnetic resonance imaging; PEGR, Patient Evaluation of Global Response.

Patients will be withdrawn for the follow-up during a 24-week observation period if they meet any of the following three conditions: (1) the subject receives a BoNT-A reinjection during the follow-up period, (2) the JRS score returns to the baseline score, or (3) completion of a 24-week follow-up visit.

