### Statistical analysis

2.10

Trial analysis will be performed on an intention-to-treat (ITT) population. No interim analyses will be performed. A full statistical analysis plan will be developed before the final analysis.

Assumptions for parametric tests will be evaluated before analysis. Normality will be assessed using the Shapiro–Wilk test and Q-Q plots, and homogeneity of variances with Levene’s test. If these assumptions are not met, non-parametric alternatives will be used.

Missing data will be handled under the ITT principle, using all available observations without imputation beyond the last completed visit. Mixed-effects models will be used for repeated-measures secondary outcomes under the missing-at-random assumption. A per-protocol sensitivity analysis will also be conducted.

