#### Primary endpoint analysis

2.10.2

The primary outcome metric of the study, which is the duration of effective symptom relief as measured by the JRS severity subscale, will be analysed using a *t*-test or Mann–Whitney U-test to compare the differences between the two groups. The difference and its 95% confidence interval (CI) are also reported.

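### The primary duration is tested by t-test or Mann–Whitney with no usable rule for participants who leave while still improved; if their durations are cut at the last visit, power could fall well below 80%

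*Protocol article*

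**What the plan says.** Section 2.10.2 describes "The primary outcome metric of the study, which is the duration of effective symptom relief as measured by the JRS severity subscale" and compares the arms by t-test or Mann–Whitney U-test, reporting the difference with a 95% CI. No censoring or time-to-event method is named.

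Section 2.10 sets an ITT population and this rule: "Missing data will be handled under the ITT principle, using all available observations without imputation beyond the last completed visit". Mixed-effects models are assigned to repeated-measures secondary outcomes, so they do not cover the primary endpoint. A per-protocol sensitivity analysis and a later full SAP are announced.

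The protocol foresees observation stopping before benefit ends:

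- Section 2.6 raises the arms from 25 to 32 for loss to follow-up, without stating a rate.
- Section 2.7: "Participants who have received other treatments or participated in another program related to BSP therapy during the trial will be considered dropouts".
- Section 2.9: "Data will be collected from all participants until they complete the 24-week follow-up period or discontinue the study". The same section ends follow-up at BoNT-A reinjection, at return of the JRS score to baseline, or at week 24.

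**The concern.** A participant last seen improved at week 4 who then leaves has a duration of at least 28 days and otherwise unknown. Neither named test can use a value of the form *at least 28 days*. Two treatments of this participant fit the text:

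- **Cut:** enter 28 days. This keeps everyone in the ITT set but treats leaving as loss of benefit.
- **Leave out:** no completed duration, no entry. This fits the words about available observations, but it abandons ITT.

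Cutting brings short values unrelated to treatment into both arms, which inflates the SD and pulls the difference towards zero. Leaving out is safe only if departure is unrelated to benefit. Participants know their oil, and someone whose benefit is waning may seek other treatment and so be labelled a dropout. The choice affects the only primary comparison and, as written, could be made after the data are seen.

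**Working it through.** **Inputs (section 2.6).** "The sample size was calculated using the two-sample t-test method in PASS 15 software", "with a two-sided significance level of 0.05 and a power of 0.8". Control: "we decided to round the mean value to 75 days and the SD to 15". Experimental: "we estimated the mean duration of benefit in the experimental group as 90.0 ± 18.5 days", built from a 50% share of responders at 105 ± 15 days. The difference is 90 − 75 = 15 days. Follow-up is 24 × 7 = 168 days.

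**Step 1: reproduce the stated size.** n per arm = 2(1.96 + 0.8416)² SD²/Δ². With SD 18.5 in both arms: 2 × 7.849 × 342.25/225 = 23.9, so 24 by normal approximation and 25 by the exact t calculation (power 0.802). The stated 25 is reproduced. At 32 per arm with no loss, power is 0.89.

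**Step 2: implied loss.** 1 − 25/32 = 21.9%; equally, 25/(1 − 0.20) = 31.25, rounded up to 32. This is an allowance used here as an assumed rate. The timing of loss is not in the document, so it is varied.

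**Step 3: week-24 censoring.** (168 − 105)/15 = 4.2 SD and (168 − 90)/18.5 = 4.2 SD. It is negligible under the planning figures; the problem lies in earlier departures.

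**Step 4: simulation.** 32 per arm, 2,000 trials per setting, non-informative dropout equal in both arms, visits at weeks 2, 4, 8, 12, 16, 20 and 24. Three duration models were used: 75 ± 15 v 90 ± 18.5; SD 18.5 in both arms; and a 50:50 responder mixture. The ranges cover these models. For 21.9% spread loss they also include a mixture run in which every duration is taken as the last improved visit.

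| Durations cut at last completed visit | t-test | Mann–Whitney |
|---|---|---|
| 21.9% loss, spread over 24 weeks | 0.55–0.58 | 0.61–0.75 |
| 21.9% loss, all before benefit ends | 0.43–0.46 | 0.52–0.62 |
| 21.9% loss, all in first 8 weeks | 0.30–0.32 | 0.43–0.51 |
| 10% loss (SD 18.5 in both arms) | 0.64–0.74 | 0.76–0.80 |
| 5% loss (SD 18.5 in both arms) | 0.74–0.80 | 0.81–0.83 |

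In the mixture model with every duration taken as the last improved visit, 5% loss gives about 77% by either test.

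**Step 5: mechanism.** With SD 18.5 and spread loss of 21.9%, the mean difference is 13.1 days and the SD 24.6. By normal approximation, power = Φ(Δ/(SD√(2/32)) − 1.96):

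- no loss: 15/4.625 = 3.24, power 0.90
- smaller difference only: 13.1/4.625 = 2.83, power 0.81
- larger SD only: 15/6.15 = 2.44, power 0.68
- both: 13.1/6.15 = 2.13, power 0.57, in line with the simulated 0.56

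The larger SD does most of the damage.

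**Step 6: alternatives at 21.9% loss.** With participants lost while still improved left out, t-test power is about 0.75–0.91, depending on model and on rounding to visits. With the same participants censored, a log-rank test gives 0.74–0.93 depending on the model. In the mixture with durations read at visits, log-rank gives about 0.82, and the restricted mean comparison 0.81 with a difference of 14.9 days.

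**The case against.** A reader might infer that the protocol counts dropouts as the end of benefit and that its 80% power is therefore lost. The text does not say so. The missing-data sentence also allows participants without a completed duration to be left out, and the increase from 25 to 32 suggests that about 25 evaluable participants per arm were intended. On that reading t-test power stays near plan. This objection stands, so the power figures must be stated conditionally.

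Four further limits also stand:

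- The 21.9% is inferred, and at 5% loss the shortfall is small or absent.
- Some of the loss in the mixture runs is rounding to visits. With no dropout at all, scoring duration as the last improved visit lowers t-test power from about 90% to 85%, and the protocol does not state that scoring.
- Return of the JRS score to baseline largely coincides with the event, so that exit is mostly not censoring.
- The simulations contain only random dropout and give no figure for reinjection or other treatment.

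It can also be said that scoring details belong in the SAP. That is fair for details. But the protocol itself fixes tests that cannot take a censored value, together with a missing-data rule that does not supply one. A SAP that keeps both cannot resolve the conflict.

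**Conclusion.** The point holds in conditional form. The named primary tests do not fit a time to loss of benefit when some participants leave while still improved, and the ITT and missing-data wording gives no valid value for them.

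If durations are cut at the last visit, 22% loss spread over follow-up leaves about 55–58% power by t-test and 61–75% by Mann–Whitney. This rests on the planning means and SDs, on loss unrelated to outcome and equal in both arms, and on a loss rate inferred from 25 and 32.

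If these participants are left out, t-test power is near 80%, but the ITT claim is lost and selection is possible. Whether departures would in fact be related to waning benefit, or differ by arm, cannot be determined from the document; it is a risk and has not been shown. That the trial is underpowered outright, or that the week-24 limit distorts the result, is not supported.

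**What to change.** Amend sections 2.10 and 2.10.2, and carry the change into the SAP before the data are analysed:

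- Define the primary analysis as time to loss of the ≥1-point JRS-severity improvement, tested by log-rank or, given visits four weeks apart from week 4 onwards, by an interval-censored method.
- Report the difference in restricted mean duration to 168 days with its 95% CI, which keeps the result in days. Use a permutation reference for its test: with a normal reference, simulated type I error was about 7% at 32 per arm.
- Censor loss to follow-up at the last visit with improvement, and censor at week 24.
- State how BoNT reinjection or other BSP treatment while still improved is counted in the analysis, for example as end of benefit in the primary analysis and censored in a sensitivity analysis. Reconcile this with the dropout label in section 2.7.

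The cost is wording and a little more analysis work; no new data or patients are needed. The drawback is that the primary test then differs from the t-test behind the sample size. Its power should be restated, since the log-rank figures run from 0.74 to 0.93 by model.

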#### Baseline demographic characteristics

2.10.1

Age, educational level, MMSE, HAMA, and HAMD scores will be expressed as mean and SD for normally distributed variables or median and interquartile range (IQR) for non-normal continuous variables. Differences between the two groups will be compared using the *t*-test or Mann–Whitney U-test, as appropriate. Sex will be expressed as frequencies and percentages, and the sex distribution of the participants will be compared using the Pearson *χ*^2^ test or Fisher’s exact test.

#### Primary endpoint analysis

2.10.2

The primary outcome metric of the study, which is the duration of effective symptom relief as measured by the JRS severity subscale, will be analysed using a *t*-test or Mann–Whitney U-test to compare the differences between the two groups. The difference and its 95% confidence interval (CI) are also reported.

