### Trial design

2.1

We will conduct a single-centre, open-label, randomised controlled trial. Patients diagnosed with BSP receiving BoNT treatment at our centre will be approached. The protocol follows the Standard Protocol Items: Recommendations for Interventional Trials guidelines (22). Outcomes, including symptom severity, disability, and quality of life, will be evaluated at baseline and at weeks 2, 4, 8, 12, 16, 20, and 24 post intervention. Patients will be asked to complete a self-report questionnaire to document their response to BoNT and the duration of clinical benefits after BoNT treatment. We will recruit only those patients who have received positive benefits from BoNT for less than 12 weeks. We plan to enroll 64 patients and randomly (1:1) assign them to the experimental group (topical FEO combined with BoNT-A injection) or control group [topical coconut oil (CO) combined with BoNT-A injection]. CO will be used as the control because FEO must be diluted 1:1 with CO as the carrier oil (16).

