### Study population

2.2

All patients who meet the following inclusion criteria will be included: (1) age 18–70 years; (2) a diagnosis of BSP established according to the published criteria by a senior neurologist (2); (3) a Jankovic Rating Scale (JRS) frequency sub-score of ≥3; (4) documented history of at least three subsequent injection cycles or prospective documentation of one injection cycle of BoNT with less than 12 weeks duration of positive benefits with BoNT by a BoNT-experienced physician (23); (5) written consent obtained from participants. The exclusion criteria include: (1) family history or diagnosis of hereditary dystonia, acquired dystonia, tardive dyskinesia, or functional movement disorders; (2) presence of acute intracranial disease (e.g., stroke, intracranial infection) or history of psychiatric disorders, dementia, epilepsy, multiple sclerosis, tic disorder, Parkinson’s disease, severe traumatic brain injury, or other neurological diseases; (3) significant cognitive impairment; (4) exposure to neuroleptics; (5) contraindication to magnetic resonance imaging (MRI).

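### The primary comparison is unadjusted, so it forgoes precision that prior-cycle BoNT duration and baseline JRS severity, both already collected, could give

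*Protocol article*

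**What the plan says.** The primary analysis (Protocol article, 2.10.2) takes "The primary outcome metric of the study, which is the duration of effective symptom relief as measured by the JRS severity subscale" and compares the arms by a t-test or Mann–Whitney U-test, reporting the difference with a 95% confidence interval. Neither that section nor the rest of 2.10 names a covariate for this comparison.

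Two pre-treatment measures are available for every participant:

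- **Prior-cycle duration of BoNT benefit.** Inclusion criterion 4 (2.2) requires "documented history of at least three subsequent injection cycles or prospective documentation of one injection cycle of BoNT with less than 12 weeks duration" of benefit. A self-report questionnaire (2.1) is also used "to document their response to BoNT and the duration of clinical benefits after BoNT treatment".
- **Baseline JRS severity.** Severity is rated at baseline (2.4, Table 2), and improvement is defined relative to that score (2.3).

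Section 2.6 takes prior-cycle duration in 61 clinic patients who met the inclusion criteria (mean 73.99 days, SD 14.28) as the source of the control-arm planning value: "we decided to round the mean value to 75 days and the SD to 15".

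**The concern.** When a prognostic baseline measure is available before randomisation, adjusting for it narrows the confidence interval for the treatment difference and corrects for chance imbalance between the arms, with no extra patients. Prior-cycle duration is an obvious candidate, because the protocol already relies on it to predict how long the control arm will benefit. Baseline JRS severity is another, because it is the reference against which improvement is judged.

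The plan uses neither. Randomisation (2.7) splits 64 random numbers equally between the arms and describes no stratification. The baseline comparisons listed in 2.10.1 include neither measure. Imbalance in them is therefore neither prevented by design nor corrected in the primary analysis. At stake is the width of the interval for the primary result, not its validity.

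**Working it through.** **Inputs from section 2.6.** The design is "with a two-sided significance level of 0.05 and a power of 0.8". The method: "The sample size was calculated using the two-sample t-test method in PASS 15 software". Control arm 75 days, SD 15. Experimental arm: "we estimated the mean duration of benefit in the experimental group as 90.0 ± 18.5 days". The difference is therefore 15 days. Result: "25 participants are required for each group", with 32 per arm recruited.

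**The plan's own figure.** With noncentral-t power and a difference of 15 days:

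- A common SD of 18.5 in both arms gives 25 per arm (power 0.802; 24 per arm gives 0.785). This matches the stated figure.
- The two stated SDs, 15 and 18.5, give 21 per arm.
- Allowance for loss: 25 / 0.80 = 31.25, so 32. The loss rate is not stated; 20% is inferred.

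**Unadjusted power at 25 per arm.**

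- Stated SDs: SE = sqrt((15² + 18.5²)/25) = sqrt(567.25/25) = 4.76 days; power 0.87.
- Full 50:50 mixture of 75 ± 15 and 105 ± 15: the SD is sqrt(15² + 15²) = 21.2, which the protocol does not state. SE = sqrt((225 + 450)/25) = 5.20 days; power 0.81.

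**Effect of adjustment.** Let rho be the control-arm correlation of the covariate(s) with on-trial duration. The protocol gives no value, so a range is assumed. With the same slope in both arms, adjustment removes 225 × rho² from the variance in each arm. It does not shrink the extra experimental-arm variance, because that reflects who responds to FEO, and duration under earlier BoNT alone need not predict this.

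| rho | Variance removed | SE, SDs 15/18.5 | Power | SE, SDs 15/21.2 | Power |
|---|---|---|---|---|---|
| 0 | 0 | 4.76 | 0.87 | 5.20 | 0.81 |
| 0.2 | 9.00 | 4.69 | 0.88 | 5.13 | 0.82 |
| 0.3 | 20.25 | 4.59 | 0.89 | 5.04 | 0.83 |
| 0.5 | 56.25 | 4.26 | 0.93 | 4.74 | 0.87 |

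Example, rho 0.5 with the stated SDs: (225 − 56.25) + (342.25 − 56.25) = 454.75, and sqrt(454.75/25) = 4.26. With the stated SDs, the SE, and hence the interval width, falls by about 2%, 4% and 10% at rho 0.2, 0.3 and 0.5. Allowing for the two extra degrees of freedom changes power by less than 0.001.

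**Chance imbalance.** If prior duration has SD 14.28 and 32 are randomised per arm, the SE of the between-arm difference is 14.28 × sqrt(2/32) = 3.57 days. An imbalance of 5 days or more in either direction, a third of the 15-day target, has a probability of about 16%.

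**The case against.** The strongest reply is that nothing here is an error. Under randomisation a two-group test is unbiased and keeps its type I error, its standard error already allows for chance imbalance, and it matches the method used to size the trial. That stands: this is a point about efficiency.

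A second reply is that covariates belong in the SAP, which 2.10 says is still to come. This stands in part. However, 2.10.2 already names the primary test, and the Mann–Whitney alternative takes no covariates, so the stated method would have to change.

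A third reply is that the correlation may be weak. Prior duration is documented by a physician or reported by the patient, whereas the trial outcome is defined on JRS severity and read at visits 2 to 4 weeks apart. Eligibility caps prior duration at under 12 weeks. Some participants enter on three cycles and some on one, so the measure's reliability varies. All of this stands and is why the range starts at 0.2. Against it, the SD of 14.28 comes from patients already under the cap, so real spread remains.

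A reader might go further and infer any of the following; the documents support none of them:

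- *That power is 80% at best.* It is 0.87 at 25 per arm with the stated SDs, and 0.94 if all 32 per arm are analysed. The lower 0.81 needs both the full loss and an SD of 21.2.
- *That prior duration is the baseline value of the same outcome.* It is a related measure with a different definition.
- *That a material imbalance is likely.* A gap above 0.5 SD has about a 5% chance at 32 per arm; imbalance is plausible, not expected.

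**Conclusion.** The point holds as a loss of precision in a method the protocol has already named. On the stated SDs, adjustment would raise power at 25 per arm from 0.87 to about 0.88, 0.89 or 0.93 for rho 0.2, 0.3 or 0.5. On the assumed experimental SD of 21.2 it would rise from 0.81 to about 0.82, 0.83 or 0.87. Below rho of about 0.2 there is almost nothing to gain.

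These figures assume a linear model, a slope common to both arms, and a correlation that the documents do not give. Rho can be read as the joint correlation of both covariates with duration; no separate gain for baseline JRS severity can be worked out from the protocol. The figures do not carry over to a time-to-event model or to the Mann–Whitney test. The planned analysis is not biased, and on its own assumptions the trial reaches its 80% target without adjustment.

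**What to change.** In 2.10.2 and in the SAP, before any outcome data are seen, make the primary analysis a linear model of duration on arm, mean duration of benefit over the qualifying BoNT cycle or cycles, and baseline JRS severity. Report the adjusted difference with its 95% confidence interval, and keep the unadjusted test as a sensitivity analysis. If the primary analysis becomes a time-to-event model, use the same two covariates there.

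The cost is wording and two degrees of freedom, with no new patients and no new data. Prior-cycle duration should be held in the database as a number, not only as an eligibility tick. Timing matters, because covariates added after outcomes are known look chosen for their effect on the result.
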